**Discussion:** The CaRe-ECMO is designed to answer the question “whether cardiopulmonary rehabilitation can facilitate weaning of ECMO (CaRe-ECMO).” Should the implementation of the CaRe-ECMO program result in superior primary and secondary outcomes as compared to the controls, specifically the add-on effects of cardiopulmonary rehabilitation to the routine ECMO practice for facilitating successful weaning, the CaRe-ECMO trial will offer an innovative treatment option for ECMO-supported patients and meaningfully impact on the standard care in ECMO therapy.

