Key secondary outcomes	Rate of ECMO weaning, total length of ready for ECMO weaning, total length of ECMO weaning, rate of mechanical ventilation weaning, total length of mechanical ventilation, all-cause mortality, rate of major post-ECMO complications, ECMO Unit LOS, total hospital LOS, total cost for hospitalization, CPC, ADL, and HRQoL

*CaRe-ECMO, cardiopulmonary rehabilitation on extracorporeal membrane oxygenation; LOS, length of stay; CPC, cerebral performance category; ADL, activities of daily living; HRQoL, health-related quality of life*.

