#### Secondary Outcomes

Secondary outcomes are listed and elaborated as follows:

1) Rate of ECMO weaning will be calculated according to date of ECMO weaning fulfilled.2) Total length of ready for ECMO weaning refers to exact length in day till patients fulfill all the criteria of ready for ECMO weaning according to daily checkout records (14).3) Total length of ECMO weaning refers to exact length in day for patients treated with ECMO therapy (29).4) Rate of mechanical ventilation weaning will be calculated according to date of mechanical ventilation weaning fulfilled. Daily screening of mechanical ventilation weaning will be strictly performed with checklist shown in Table 7 according to the American Thoracic Society and the American College of Chest Physicians Clinical Practice Guideline (30).5) Total length of mechanical ventilation refers to exact length in day for patients treated with mechanical ventilation.6) All-cause mortality is defined as rate of death due to any causes and will be calculated according to date of death (31).7) Rate of major post-ECMO complications refers to rate of complications occurred after ECMO including but not limited to ECMO-related complications (e.g., thromboembolism), mechanical ventilation-related complications (e.g., pneumonia), newly developed myocardial infarction, acute kidney injury, neurologic events (e.g., stroke, seizures), and multiple organ failure (32). Information of major post-ECMO complications will be collected in the Complication Recording Sheet (Table 8).8) Diaphragmatic thickness and mobility refer to ultrasound-guided evaluation of diaphragmatic thickness and mobility under M-mode (33).9) Extracorporeal membrane oxygenation unit LOS accounts for length in day for stay of patients in the ICU unit.10) Total hospital LOS accounts for total hospital LOS in day for stay of patients in both the ECMO unit and other departments.11) Total cost for hospitalization will be calculated by addition of the cost of all the units and department admission.12) Cerebral performance category will be recorded, for those successfully weaning of ECMO, to reflect post-ECMO neurological status (34).13) Activities of daily living will be evaluated, for those successfully weaning of ECMO, with Katz Index (35).14) Health-related quality of life will be measured, for those successfully weaning of ECMO, with SF-12 (36).

**Table 7 T7:** Mechanical ventilation weaning checklist.

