### Data Collection

Data in terms of rate of ready for ECMO weaning, rate of ECMO weaning, rate of mechanical ventilation weaning, all-cause mortality, and rate of major post-ECMO complications will be calculated throughout the index hospitalization and follow-up period (e.g., CaRe-ECMO days 7, 14, 30, and 90) according to daily evaluations recorded in the medical records. Outcomes, for instance ready for ECMO weaning, will be treated as time-to-event outcomes; therefore, date and timing of events will be also recorded to facilitate statistical analysis. Total length of ready for ECMO weaning, total length in hour of ECMO weaning, total length in day of mechanical ventilation, ECMO unit LOS, and total hospital LOS will be collected according to the medical records. CPC index, ADL score, and HRQoL score will be selectively collected among those successfully weaning of ECMO across discharge day (discharge from ECMO unit) and all follow-up time points (e.g., CaRe-ECMO days 30 and 90). In addition, diaphragmatic thickness and mobility will be evaluated with ultrasound (M-mode) every 3 days for determining the allocation of phrenic nerve and the efficacy of SEPNS. The detailed data collection schedule is given in Table 9.

**Table 9 T9:** Scheduled events and timeline of the CaRe-ECMO trial.

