### Statistical Methods

The demographic and clinical characteristics collected at randomization will be presented as means with SDs or medians with interquartile ranges for continuous variables and as percentages for categorical variables, as appropriate.

For all the outcomes, we will estimate differences in effect size between the groups on both the intention-to-treat (ITT) and per protocol (PP) basis (39). Categorical variables will be compared with the chi-square or Fisher's exact tests and continuous variables will be compared with the Student's *t*-test or the Wilcoxon signed-rank test, as appropriate. The time effect of day the time-to-event outcomes identified (e.g., rate of ready for ECMO weaning, rate of ECMO weaning, rate of mechanical ventilation weaning, all-cause mortality, and rate of major post-ECMO complications) between the groups will be estimated with the Cox proportional hazards regression analysis and graphically illustrated using the Kaplan–Meier methods until CaRe-ECMO days 7, 14, 30, and 90, respectively (40). Variables, including total length of ready for ECMO weaning, total length of ECMO weaning, total length of mechanical ventilation, ECMO unit LOS, and total hospital LOS, will be treated with time-to-event data and will be analyzed with mixed-effects ordered logistic regression (41). Secondary outcomes with normal and non-normal distributions, including CPC, ADL, HRQoL, and diaphragmatic thickness and mobility, will be estimated for group differences with mixed-effects linear regression (41).

Considering that part of patients will definitely not reach the primary endpoint, i.e., ready for ECMO weaning at CaRe-ECMO day 7 for sensitivity purpose, we will assess the heterogeneity of the treatment effect on primary outcome and secondary outcomes in pre-specified subgroups of interest as per baseline data to be collected at randomization (e.g., age, gender, main diagnosis, comorbidities, the APACHE II score, ECMO mode, length since mechanical ventilation) by using exploratory *post-hoc* sensitivity adjusted analyses for any corresponding statistical methods mentioned above.

Interim analysis will be scheduled halfway through enrollment to check that there are no serious issues with respect to sample handling or data collection.

All the analyses will be conducted at a two-sided alpha level of 5% and will be performed using the Stata version 16 (StataCorp, College Station, Texas, USA) or other software, as appropriate.

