To sum up, the currently proposed CaRe-ECMO trial is a pragmatic, multidisciplinary, randomized controlled, parallel group, clinical trial, designed to answer the question whether cardiopulmonary rehabilitation can facilitate weaning of ECMO. Should the implementation of the CaRe-ECMO program result in superior primary and secondary outcomes as compared to the controls, the CaRe-ECMO trial will offer an innovative treatment option for ECMO-supported patients and meaningfully impact the standard care in ECMO therapy.

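### All 14 secondary outcomes are tested at a flat two-sided 5% with no order and no supportive label, while the conclusion about standard care cites superiority on them

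*Protocol article*

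**What the plan says.** The Secondary Outcomes section opens with "Secondary outcomes are listed and elaborated as follows" and numbers 14 items. Table 1, under Trial Design, puts 13 of them under "Key secondary outcomes" with no ranking. The one missing there is diaphragmatic thickness and mobility.

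Statistical Methods analyses every outcome on both the intention-to-treat and the per-protocol set and does not say which one leads. The rate outcomes (readiness, ECMO weaning, ventilator weaning, mortality, complications) go through Cox models and are "graphically illustrated using the Kaplan–Meier methods until CaRe-ECMO days 7, 14, 30, and 90, respectively". The level is fixed for everything: "All the analyses will be conducted at a two-sided alpha level of 5" per cent. In that section the word exploratory is attached only to the subgroup analyses.

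The Discussion closes with a conditional sentence that begins "Should the implementation of the CaRe-ECMO program result in superior primary and secondary outcomes as compared to the controls" and ends with an effect on standard care. The Abstract has the same sentence, ending "meaningfully impact on the standard care in ECMO therapy". Neither says which secondary outcomes, how many, or at which time point.

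**The concern.** The article states a rule, so this is more than a gap that an analysis plan might fill. Every secondary analysis gets the full 5%, and the secondaries then reappear in the condition for affecting practice. With many outcomes and repeated looks, one nominal p-value below 0.05 could be offered as meeting the secondary half of that condition.

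The case that matters is a trial that succeeds on readiness for weaning but has no effect on mortality, stay, cost or function. Requiring a significant primary then gives the secondaries little protection. A chance finding on one of them could be reported as demonstrated superiority.

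No secondary effect is a plausible state of affairs. The Discussion says the randomised part is designed to power the primary. Under Interventions, non-responders in both arms are offered open-label rehabilitation after the day-7 assessment, and the Discussion concedes that this may impair long-term comparisons.

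**Working it through.** The article states no familywise error rate for the secondaries, so there is no figure of its own to reproduce. The calculation shows what the flat rule implies.

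**Inputs from the article**
- Level: two-sided 5% for each analysis (Statistical Methods).
- Secondary outcomes: 14 (Secondary Outcomes).
- Time points for rate outcomes: four, "until CaRe-ECMO days 7, 14, 30, and 90, respectively" (Statistical Methods).
- Power for the primary: 80% (Sample Size Calculation).

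**Input assumed:** the correlation between test statistics. The article gives none, so I use 0 to 0.8.

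**Counting tests**
- One per outcome: 14.
- With time points: readiness at days 14, 30 and 90 (3) + ECMO weaning, ventilator weaning, mortality and complications at four time points (4 × 4 = 16) + three lengths, two stays, cost, diaphragm, CPC, ADL and HRQoL once each (10) = 29.
- Readiness at later days is not one of the 14 numbered secondaries. On the other hand, Table 9 schedules CPC, ADL and HRQoL at five visits, and Data Collection mentions discharge and "all follow-up time points (e.g., CaRe-ECMO days 30 and 90"). Leaving out readiness and counting five visits gives 4 × 4 + 3 × 5 + 7 = 38. So 29 is one reasonable count among several.
- Testing on both ITT and PP is not counted.

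**Independent tests, all secondaries null**
- Either direction: 1 − 0.95^14 = 0.512; 1 − 0.95^29 = 0.774.
- Favouring rehabilitation only: 1 − 0.975^14 = 0.298; 1 − 0.975^29 = 0.520.

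**Correlated tests, given a significant primary whose effect is real**

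Model: each secondary statistic is √ρ·G + √(1−ρ)·E, with G shared and E independent standard normals. The primary has the same form plus a mean of 1.960 + 0.842 = 2.802, which gives 80% power. I simulated 1,000,000 draws and kept those with the primary above 1.960. Each cell is the chance of at least one nominally significant secondary.

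| Tests | ρ | Favouring rehabilitation | Either direction |
|---|---|---|---|
| 14 | 0 | 0.298 | 0.512 |
| 14 | 0.5 | 0.213 | 0.316 |
| 14 | 0.8 | 0.123 | 0.140 |
| 29 | 0 | 0.520 | 0.774 |
| 29 | 0.5 | 0.305 | 0.468 |
| 29 | 0.8 | 0.159 | 0.187 |

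The ρ = 0 rows are the closed-form values.

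**Nested time points.** Days 7, 14, 30 and 90 are cumulative follow-up of the same patients, so independence between them cannot hold. With correlation 0.8 between time points of one outcome and 0 between outcomes, the 29-test figures fall from 0.520 to 0.416 (favouring rehabilitation) and from 0.774 to 0.667 (either direction).

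**Without conditioning on the primary,** 14 tests at ρ = 0.5 give 0.35 in either direction and 0.17 favouring rehabilitation.

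**The case against.** **The practice condition is joint.** A reader might infer that a secondary result alone is meant to change care. The documents do not support that, because both sentences require a superior primary and superior secondaries together. If rehabilitation did nothing at all, a false-positive primary and at least one false-positive secondary would occur together in only 2.6% to 4.5% of trials under the correlations tried. This stands, but it does not cover a real primary effect with null secondaries.

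**The article already ranks the primary first.** There is one primary, and the randomised part is powered for it. The Discussion treats a positive readiness result as a first step towards firmer outcomes, and leaves the secondaries to future trials if the primary is not significant. That is a partial hierarchy. It sets no order among the secondaries and does not say how they may be claimed after a positive primary.

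**Multiplicity rules often sit in an analysis plan.** This is true of a detailed procedure. Here, however, the article itself fixes a blanket level and words the conclusion, so a later plan would have to override both.

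**The size is easy to overstate.** A reader might infer that a false-positive secondary claim is likely. That is not supported: two-sided figures include results favouring control, which are not the harm at issue, and the highest values need independence between nested time points. Nor does the article claim a familywise rate of 5% that these figures would breach.

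**Conclusion.** The point holds as one about how secondary results may be claimed. The flat 5% rule and the wording of the conclusion leave secondary claims after a positive primary without error control. If the primary effect is real and all secondaries are null, at least one nominally significant secondary favouring rehabilitation arises with probability about 0.12 to 0.30 (14 tests) or 0.16 to 0.52 (29 tests). Counting both directions, the ranges are 0.14 to 0.51 and 0.19 to 0.77. These rest on assumed correlations from 0.8 to 0 and on the counting convention above, and the independence end is unrealistic where time points are nested.

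A reader might also infer that the trial's main type I error is inflated. It is not, because testing secondaries does not affect the single primary. The point is minor to moderate.

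**What to change.** Add to Statistical Methods: only the primary outcome supports a confirmatory claim at two-sided 5%; all secondary outcomes, at all time points, are supportive or exploratory and are reported as estimates with unadjusted 95% confidence intervals.

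In the Abstract and the closing paragraph of the Discussion, describe secondary results as supporting a positive primary, not as demonstrated superiority. Do not simply delete the secondaries from that sentence: resting the standard-care statement on readiness alone would loosen the joint condition that the article now sets.

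The cost is one sentence and two rewordings, with no extra patients or data and no loss of power for the primary. The downside is that secondary results can no longer be presented as proven benefits.

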## Discussion

Cardiopulmonary rehabilitation was proven to be effective in the improvement of cardiovascular and respiratory function in various major diseases (42). However, its efficacy in ECMO-supported patients has not been well-verified. Its application in routine clinical practice always encounters a number of challenges. Specifically, one of the major barriers is the multiple sites of cannulation, which restrict the mobilization of the body. This explained why most of the trials involved patients with VV-ECMO with cannulation sites in the upper body allowing for more chances of mobilization while less on VA-ECMO (4). Nonetheless, active cardiopulmonary rehabilitation is ever difficult to be performed for various reasons. In the emergency room, patients would always be sedated with the application of nitric oxide and neuromuscular blocking agents to promote oxygenation and improve ventilator synchrony. That is why, only few studies reported results with limited sample size in awake patients with ECMO (43, 44). Furthermore, active mobilization of the body may interrupt the ECMO flow (45). Therefore, the upcoming challenge is to explore a cardiopulmonary rehabilitation protocol, which can be safely delivered with no interruption of the routine clinical treatment and subsequently benefit all the types of ECMO-supported patients.

Despite the fact that most of cardiopulmonary rehabilitation carried out in the ICU and emergency room are low intensity, intensive rehabilitation has not been found to be superior to rehabilitation with relatively low intensity (46, 47). In addition, various types of cardiopulmonary rehabilitation have been documented as functional beneficial in the literature. For instance, prone positioning has been demonstrated to decrease mortality at day 28 (16.0 in the prone group vs. 32.8% in the supine group, *p*< 0.001) and day 90 (23.6 vs. 41.0%, *p*< 0.001) in patients with acute respiratory distress syndrome. Its application was strongly encouraged by several well-designed studies (27, 48). Physiotherapy such as NMES-induced muscle contraction may serve as muscle pump to increase ejection capacity and improve both the venous return and muscle perfusion, consequently compensate cardiac function (49). Moreover, ICU-acquired weakness was frequently observed in the ICU and diaphragm dysfunction developed more often than limb muscle weakness (50). Diaphragmatic weakness, occurs in as early as 18 h after mechanical ventilation, is attributed to proteolysis-induced muscle contractile dysfunction (51). It was proven to be associated with a higher rate of mechanical ventilation weaning failure and prolonged length of mechanical ventilation (52). Upon this condition, we also included electrical stimulation of phrenic nerve to minimize the reduction of diaphragm atrophy and strength over time, possibly contributing to speed up respiratory functional recovery and subsequently leading to increased rate of ECMO weaning and shortened length of ECMO therapy (53–55). Taken together, it is reasonable to hypothesize that our protocolized cardiopulmonary rehabilitation may contribute to internal pathophysiological changes (e.g., cardiac output and maximal oxygen uptake) and spread it to external clinical outcomes (e.g., earlier weaning of ECMO and increased rated of ECMO weaning).

Additional important considerations, which we addressed when preparing the CaRe-ECMO trial protocol, were the following. First, the current trial is consisting of a RCT part followed by an open-label cohort part. According to our clinical experience and retrospective data analysis, the median length of ECMO weaning varied ~from 7 to 9 days in all the types of ECMO-supported patients. The design rationale of the RCT part is to power the primary outcome, while the following open-label cohort part is dedicated to benefit patients who do not respond to one cycle of cardiopulmonary rehabilitation. This action may impair the effects of RCT on long-term outcome observation; however, it is hypothesized to provide additional opportunity for those who are probably benefitted from active intervention (56). Second, a critical concern of the CaRe-ECMO trial design is the uncertainty of the effect size of the proposed interventions. Therefore, our attention on primary outcome selection has been shifted from the exact ECMO weaning to ready for ECMO weaning. If any significant results would be introduced in terms of earlier ready for ECMO weaning or increased rate of ready for ECMO weaning due to our proposed interventions, then it may satisfy the preliminary requirements when extending its effects to more consolidated outcomes (e.g., rate of ECMO weaning). To compensate the aforementioned risks, we introduce several evidence-based checklists to ensure the standardized definition and evaluation of ECMO or mechanical ventilation weaning (Tables 5–7) and to maximally avoid potential performance bias. Third, functional outcomes are essential to the long-term recovery; therefore, CPC index, ADL score, HRQoL score, and diaphragmatic thickness and mobility will be consecutively collected. In case when primary outcome of the CaRe-ECMO trial does not show a statistically significant difference, future trials may consider to analyze our secondary clinical and functional outcomes.

To sum up, the currently proposed CaRe-ECMO trial is a pragmatic, multidisciplinary, randomized controlled, parallel group, clinical trial, designed to answer the question whether cardiopulmonary rehabilitation can facilitate weaning of ECMO. Should the implementation of the CaRe-ECMO program result in superior primary and secondary outcomes as compared to the controls, the CaRe-ECMO trial will offer an innovative treatment option for ECMO-supported patients and meaningfully impact the standard care in ECMO therapy.

## Data Availability Statement

The original contributions presented in the study are included in the article/supplementary material, further inquiries can be directed to the corresponding author/s.

## Ethics Statement

The studies involving human participants were reviewed and approved by the First Affiliated Hospital of Nanjing Medical University (Reference number of 2021-SR-416). The patients/participants provided their written informed consent to participate in this study.

